## Abstract

**Background:**

The prevalence of multimorbidity (the presence of two or more chronic health conditions) is rapidly increasing in sub–Saharan Africa. Hospital care pathways that focus on single presenting complaints do not address this pressing problem. This has the potential to precipitate frequent hospital readmissions, increase health system and out-of-pocket expenses, and may lead to premature disability and death. We aim to present a description of inpatient multimorbidity in a multicentre prospective cohort study in Malawi and Tanzania.

**Primary objectives:**

Clinical: Determine prevalence of multimorbid disease among adult medical admissions and measure patient outcomes. Health Economic: Measure economic costs incurred and changes in health-related quality of life (HRQoL) at 90 days post-admission. Situation analysis: Qualitatively describe pathways of patients with multimorbidity through the health system.

**Secondary objectives:**

Clinical: Determine hospital readmission free survival and markers of disease control 90 days after admission. Health Economic: Present economic costs from patient and health system perspective, sub-analyse costs and HRQoL according to presence of different diseases. Situation analysis: Understand health literacy related to their own diseases and experience of care for patients with multimorbidity and their caregivers.

**Methods:**

This is a prospective longitudinal cohort study of adult (≥18 years) acute medical hospital admissions with nested health economic and situation analysis in four hospitals: 1) Queen Elizabeth Central Hospital, Blantyre, Malawi; 2) Chiradzulu District Hospital, Malawi; 3) Hai District Hospital, Boma Ng’ombe, Tanzania; 4) Muhimbili National Hospital, Dar-es-Salaam, Tanzania. Follow-up duration will be 90 days from hospital admission. We will use consecutive recruitment within 24 hours of emergency presentation and stratified recruitment across four sites. We will use point-of-care tests to refine estimates of disease pathology. We will conduct qualitative interviews with patients, caregivers, healthcare providers and policymakers; focus group discussions with patients and caregivers, and observations of hospital care pathways.

## Introduction

### Background and rationale

Non-communicable diseases (NCDs), which can be accelerated by human immunodeficiency virus (HIV) infection and its therapy, are a major health problem in sub-Saharan Africa (sSA)
^
1
^. Diagnosis is frequently delayed until emergency hospital presentation, when people are already severely unwell
^
2
^. In hospitals, unrecognised multimorbidity (“the co-existence of two or more chronic conditions”
^
3
^ results in frequent re-admission, high out-of-pocket expenses, disability and preventable death
^
4
^. In sSA, co-existent infectious and non-communicable disease pathology is common
^
5
^. Some studies suggest a higher burden of multimorbidity among females compared to males
^
6,
7
^. Existing risk stratification and screening frameworks from High Income Countries are poorly calibrated for people in sSA and underestimate severity. For example, diabetes and hypertension are more prevalent in African populations at younger ages
^
8
^. Acute medical admission is frequently the index presentation of multimorbid disease in areas of poverty
^
9
^.

The patient pathway in sSA regions may be protracted and complex
^
10
^. People frequently seek healthcare late for reasons including opportunity cost, poor health literacy and prior consultation with informal care providers. This leads to high prevalence of poorly controlled multi-morbid disease in hospital emergency care where recognition of multimorbidity is delayed or prevented by weak triage systems, resource limitations, and a focus on a single primary diagnosis
^
11
^. Commitments to Universal Health Coverage and the World Health Organization Model List of Essential Medicines
^
12
^ mean that HIV and NCDs are treatable through improved access to essential medicines. However, significant barriers include a lack of patient empowerment and health literacy, shortage of healthcare workers (HCW) and limited training
^
13
^.

Malawi (low income) and Tanzania (low-middle income) are neighbouring countries in the sub-Saharan African region that have experienced dramatic increases in life expectancy between 2000 and 2020 (Malawi 45.6 to 64.3 and Tanzania 50.8 to 65.5 years of age)
^
14,
15
^. This has been accompanied by increased rates of non-communicable diseases such as hypertension and type 2 diabetes, however, the health systems of both countries are currently weighted toward communicable disease control
^
16
^ with insufficient provision for the management of multimorbid conditions. Roll-out of anti-retroviral treatment for HIV has been a success, and as patients with HIV live longer, there is increasing risk of frequent and complex interaction between HIV and NCDs; in particular hypertension and diabetes
^
17
^.

Based on data and clinical reports of medical patient cohorts in Tanzania and Malawi, three frequently co-existing diseases warrant immediate focus: HIV infection, hypertension and diabetes
^
18–
23
^. A systematic review and meta-analysis also confirmed high prevalence of these conditions among medical in-patients in sub-Saharan hospitals (HIV: 36.4%; hypertension: 24.7%; diabetes: 11.9%)
^
24
^, however, these data are limited in scope and taken from multiple sources, targeted to single rather than multimorbid diagnoses. Chronic kidney disease was another common condition (7.7% prevalence)
^
24
^, but which lacked accurate data on chronicity. Inconsistent use of diagnostic methodology and criteria are common in sSA due to under-resourced diagnostic and laboratory services
^
24,
25
^.

### Objectives

The primary objectives of this mixed methods (clinical, health economics and qualitative) study are:

*Clinical:* Determine the prevalence of multimorbid disease in adults admitted to hospital with acute medical conditions in Malawi and Tanzania.

*Health Economic:* Measure economic costs incurred and changes in health-related quality of life between admission and 90 days post admission.

*Situation analysis:* Describe current care for multimorbidity, enabling and hindering factors to the delivery of patient centred care.

We aim to use the findings to inform the development and design of a randomised controlled trial.

The secondary objectives are:

*Clinical:*

1.Measure prevalence of important pre-selected individual conditions, including chronic non-communicable (hypertension, diabetes mellitus and chronic kidney disease) and communicable (HIV infection) conditions.2.Measure hospital readmission rate 30 and 90 days after admission.3.Measure survival 30 and 90 days after admission.4.Measure a composite of readmission free survival 30 and 90 days after admission.5.Measure markers of disease control 90 days after admission.6.Measure the rate of end-organ damage (such as cerebrovascular accident and myocardial infarction).

*Health Economic:*

1.Disaggregate economic costs from patient and health system perspectives and sub-analyse according to the presence of multimorbidity and other socio-economic factors.2.Model how patients with different multimorbidity incur costs as they pass through the health system.3.Analyse changes in Health-related Quality of Life according to presence of different diseases.4.Estimate the potential cost-effectiveness of a selected intervention to improve diagnosis and treatment for people with multimorbidity.

*Situation Analysis:*

1.Describe healthcare pathways for adults during and after acute medical admission using structured observational data during patient admission.2.Qualitatively describe (i) patients’ level of health literacy related to their own conditions and (ii) healthcare engagement for patients with multimorbidity using key-informant interviews.

### Overarching study hypothesis

For adults admitted to hospital in Malawi and Tanzania, co-existing medical conditions occur at a rate where screening is worthwhile at the individual and health system level (predefined at ≥5% prevalence).

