Other conditions are expected to contribute to multimorbidity, for example hearing and visual impairment, causes of impaired mobility such as injury at birth, or disability from trauma, surgical procedures and others later in life. A key criterion for inclusion in the planned intervention study will be potential for improved morbidity or mortality from linkage to care. We will therefore collect data on disability using standardised questionnaires, with key components from Washington Group on functioning, Patient Health Questionnaire (PHQ)-9 for depression in addition to data tools used in previous cohort studies for the collection of standardised clinical information, and allow this to inform the intervention design.

Clinical outcomes, coded from a structured case summary and the available medical notes, will be established as follows:

1.Medical diagnosis and supporting evidence.2.In-patient treatment of these diagnoses, including time of appropriate treatment establishment.3.Vital signs, including pulse oximetry (using a A310 finger oximeter), respiratory rate, pulse rate, blood pressure and temperature.4.Routine laboratory data supporting these diagnoses (such as urine lipoarabinomannan [LAM], serum CrAg).5.Clinical outcomes will also be ascertained at hospital discharge, 30 days and 90 days as:6.Death (coded from all available records).7.Readmission to hospital.

Data will be collected by a study nurse using electronic data capture. This will describe the patient characteristics, medical history and ‘patient journey’ through the healthcare system. Age, date of birth and sex will be documented from patient reports and/or clinical notes. To ensure complete data collection, we will prospectively collect data on vital signs, details of resuscitation, medication administration, results of clinical, laboratory, and radiologic examinations. All clinically relevant findings will be entered into the medical notes to ensure availability to the responsible clinicians.

As a component of the functional assessment, we will measure hand grip strength at day 90 follow-up using a GRIPX Digital Hand Dynamometer, which is a known predictor of health and overall strength
^
28
^. Grip strength will be measured seated on a chair without elbow rests, with the elbow loosely flexed at 90
^0^, and the wrist in a neutral position
^
29,
30
^. Grip strength will be measured as the mean of three tests on both hands with 60 seconds of recovery between each attempt.

**

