### Sample size

**
*Phase 1 A: Prospective longitudinal cohort study*.** The primary outcome will be disease prevalence. At 5% prevalence, a precision of 1.5% and power of 90% at α=0.05 is expected (precision will reduce as actual estimate rises towards 50%). We will use 5% prevalence as the lower boundary for inclusion of the disease during intervention development. We expect that HIV, hypertension and diabetes will meet this threshold. The cohort will allow us confidence to decide on the inclusion of chronic kidney disease. Prevalence will be assessed in both countries at the district and central hospital level to determine if findings are shared across settings. Given these assumptions, sample size is 1544 patients, with a target of 1600 to account for drop out. We will recruit these patients across the four hospitals (with numbers varying between sites due to different patient loads).

**
*Phase 1 B: Health economic evaluation*.** A randomised sub-sample of one third of the cohort study participants will be selected for participation in patient costing and HRQoL analysis (approximately 133 participants per hospital).

**
*Phase 1 C: Situation analysis*.** Sampling strategies for patients and caregivers is designed to include those individuals representing: those admitted for the first time and those who are returnees; those on HDU, ICU and ordinary wards; different age categories; male and female. We will ensure inclusion of patients with multiple known pathologies representing “multimorbidity” according to the final definition. Sample sizes for interviews are preliminary; they will continue until a point of saturation is reached.
Table 2 shows estimates of the number of patient and carer interviews required. For healthcare workers, we will include different cadres working in different departments.

**Table 2. T2:** Number of in-depth interviews, focus group discussions and structured discussions.

PER HOSPITAL SITE	In-depth interviews	Focussed group discussions	Structured discussions
Patients with multimorbidity *	10	24	10
Caregivers to patients with multimorbidity *	10	24	10
Doctors	2	-	4
Nurses	4	-	8
Ward attendants	2	-	6
Reception / frontline administration staff	2	-	2
Total	30	48	40

* Patients and caregivers will not be the same group during IDIs and FGDs. IDI, In depth interviews; FGD, focus group discussion.

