### Data management

Consent will be documented on paper or electronic forms. A paper copy will be given to the participant or guardian, and any original paper will be stored in a locked cabinet at the local hospital site, accessible only to the study team. All study data will be collected electronically.

Baseline, follow-up questionnaire data, and physiological observations (including pulse, respiratory rate, blood pressure, and oxygen saturations), and any point-of-care measures will be captured direct to Open Data Kit
^
32
^ software on devices with password encryption.

Clinical information including presenting complaints, history of presenting complaints, past medical history and drug history will be collected. Data on differential diagnosis and final diagnosis will be collected including clinical actions (
*e.g.*, prescribed medication) and patient response. We will also collect information on prescribed medication at hospital discharge, including where possible out of pocket expenses, health literacy and drug dispensary access (including stock outs).

Laboratory test results will be directly electronically exported from laboratory information systems where possible.

The study will adhere to LSTM (sponsor) data management and security policies, and encryption guidelines. This allows the data from each site to be collated, and presented at summary level in near real-time for the purposes of monitoring recruitment across both countries. During the study, individual participant level data will be available by the study team only, for the purposes of data validation and completeness checking. Access to this will be controlled by the same data security policies, with journaling of data change requests to allow full data audit.

After successful import of external data, and formal closure of the study, data will be fully anonymised by removing identifiers (including embedded electronic data) and granulating data which might enable an individual to be triangulated (area of habitation will be retained at “ward” level, and age rounded to the nearest year).

Data management for the patient costs, and HRQoL will be as per the clinical cohort study. Health system cost data will be collected and stored in custom built Excel spreadsheets.

**

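### Total prevalence of 5% or more is taken to show that screening is worthwhile, but total prevalence does not measure what screening would add

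*Protocol article*

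**What the plan says.** The Overarching study hypothesis section states that "co-existing medical conditions occur at a rate where screening is worthwhile at the individual and health system level (predefined at ≥5% prevalence"). The only input is prevalence; the conclusion is about the worth of screening.

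The Sample size section (Phase 1 A) uses the same figure for a second purpose: "We will use 5% prevalence as the lower boundary for inclusion of the disease during intervention development". It then says "We expect that HIV, hypertension and diabetes will meet this threshold" and leaves only CKD to be decided by the cohort.

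The prior figures are in Background and rationale: "HIV: 36.4%; hypertension: 24.7%; diabetes: 11.9"%, and 7.7% for CKD, with the caveat that the CKD figure lacked accurate data on chronicity.

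Known cases are not set apart. The exclusion criteria do not remove patients with an established diagnosis, the Analysis section reports prevalence without a split into known and new, and the Table 1 note on HIV testing allows the diagnosis to rest on an earlier test.

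Two other statements bear on the point. Data sources and measurement says: "A key criterion for inclusion in the planned intervention study will be potential for improved morbidity or mortality from linkage to care". Data management says: "Clinical information including presenting complaints, history of presenting complaints, past medical history and drug history will be collected".

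**The concern.** Screening adds only the cases that were not already known. The protocol's own rationale is unrecognised multimorbidity and diagnosis delayed until emergency presentation, and total prevalence measures neither. Two hospitals with the same HIV prevalence, one with nearly all patients already diagnosed and the other with few, would give the same result under the hypothesis, although screening would yield very different numbers of new cases.

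What is at stake is the conclusion the study may draw. Followed as written, it could report that screening is worthwhile for individuals and the health system from a figure that carries no information on yield. For three of the four conditions that figure is expected in advance to pass.

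**Working it through.** **The plan's own figure.** The Sample size section states: "At 5% prevalence, a precision of 1.5% and power of 90% at α=0.05 is expected" and "Given these assumptions, sample size is 1544 patients, with a target of 1600 to account for drop out". Sidedness and comparator are not given. A one-sided one-sample test of 5% against 3.5% comes close:

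n = [1.645·√(0.05·0.95) + 1.282·√(0.035·0.965)]² / 0.015² = 1569.

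The arcsine version gives 1538, and the exact binomial (null 3.5%, alternative 5%) gives 1548. So 1544 is reproduced within 2%. The point does not depend on it; n = 1544 is used below.

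**When the rule is met.** 0.05 × 1544 = 77.2, so the estimate reaches 5% with 78 or more cases. All probabilities are exact binomial, P(X ≥ 78 | 1544, p).

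**Single conditions, total prevalence.**
- HIV 36.4%, hypertension 24.7%, diabetes 11.9%: about 1.00 each.
- CKD 7.7% at face value: 0.99999. If only part of the 7.7% is truly chronic (assumption): 0.97 at 80% confirmed, 0.74 at 70%, 0.22 at 60%, 0.01 at 50%.

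**Two or more of the four conditions.** No joint figure is given. Assuming independence:
- P(none) = 0.636 × 0.753 × 0.881 × 0.923 = 0.389
- P(exactly one) = 0.389 × (0.364/0.636 + 0.247/0.753 + 0.119/0.881 + 0.077/0.923) = 0.436
- P(two or more) = 1 − 0.389 − 0.436 = 0.175; the rule is met with probability about 1.00.

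Leaving CKD out gives 14.1% for two or more of three. Cutting all four prevalences by a quarter gives 10.4%, and the rule is still met with probability above 0.999. Without independence, the single prevalences allow anything from 0% (they sum to 0.807, so need not overlap) to 0.807/2 = 40.3%.

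**Specific pairs, under independence.** HIV + hypertension 9.0%; HIV + diabetes 4.3%; hypertension + diabetes 2.9%; HIV + CKD 2.8%; hypertension + CKD 1.9%; diabetes + CKD 0.9%. Five of the six are below 5%.

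**Newly detected disease.** Let u be the share of cases undiagnosed before admission. The protocol gives no value, so u is varied. New-case prevalence is p × u, and it reaches 5% at u = 0.05/p.

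| Condition | u needed for 5% | P(new-case estimate ≥ 5%), lower u | P(new-case estimate ≥ 5%), higher u |
|---|---|---|---|
| HIV | 13.7% | 0.003 at u = 10% | about 1.00 at u = 20% |
| Hypertension | 20.2% | 0.44 at u = 20% | about 1.00 at u = 30% |
| Diabetes | 42.0% | 0.002 at u = 30% | 0.94 at u = 50% |
| CKD | 64.9% | 0.01 at u = 50% | 0.74 at u = 70% |

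In counts for HIV: about 562 cases are expected in total (0.364 × 1544). About 56 would be new at u = 10% and about 112 at u = 20%, on either side of the 78 needed. The total-prevalence rule returns the same answer in both cases.

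**The case against.** The strongest reply is that 5% does not decide the intervention alone. The Sample size section calls it a lower boundary. Data sources and measurement names benefit from linkage to care as a key criterion, the Objectives and Study phases sections plan cost-effectiveness modelling to support selection, and Phase 2 adds stakeholder review. This stands. A reader might infer that a common but already-known condition would be carried into the cluster trial on prevalence alone. The document does not support that: such a condition would pass this floor and still face the other criteria.

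A reader might also infer that the rule cannot fail. That is not supported either. The prior figures concern single conditions, and the protocol warns that they are limited in scope. Most specific pairs fall below 5% under independence. CKD, the one condition the protocol leaves open, could miss the threshold once chronicity is required. That the other three should pass is stated openly.

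Third, the programme also aims at linkage, treatment and disease control, so known but uncontrolled disease is in scope. A 5% rule on new cases only could drop a condition that the intervention could help. This is a sound reason not to replace the inclusion boundary. Undiagnosed shares may also be large, since the Background says diagnosis is frequently delayed; the working therefore shows both directions.

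Finally, splitting known from new cases may be left to an unseen analysis plan, and counting known cases is explicit only for HIV and otherwise inferred from the absence of any restriction. But the step from 5% prevalence to worthwhile screening is fixed in this document, and none of these replies removes it.

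**Conclusion.** The concern holds for the hypothesis. Total prevalence of 5% or more is predefined as showing that screening is worthwhile, and total prevalence cannot show that. The threshold is near-certain to be met for HIV, hypertension and diabetes singly if the quoted prevalences apply to these hospitals. It is also near-certain for two or more of the four conditions if they are roughly independent. It remains open for CKD and for most pairs.

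Whether newly detected disease reaches 5% depends on undiagnosed shares that the protocol does not give. Over the ranges tried, the probability runs from below 0.01 to about 1.00 for HIV and from 0.002 to 0.94 for diabetes, so the choice of measure can reverse the conclusion. The point does not extend to the 5% inclusion boundary, which is sound as a minimum beside the other criteria.

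**What to change.** 1. Restate the overarching hypothesis as a prevalence statement (prevalence of 5% or more) and drop the inference that this alone shows screening to be worthwhile.
2. Base any statement about the value of screening on conditions newly detected by study testing, meaning not in the recorded past medical or drug history at admission. Report this out of all participants with a 95% CI, for each condition and for two or more conditions with at least one newly detected.
3. Report known but uncontrolled disease separately, because linkage to care is also a target.
4. Keep the 5% total-prevalence boundary in the Sample size section, stated as a minimum only.

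The cost is a wording change and one cross-tabulation of recorded history against study test results. No further patients or tests are needed, and the Study status section says analysis has not yet been performed. The drawbacks are that the split depends on how complete the recorded history is and that the headline figure will be less favourable.
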